# Gum Chewing, Added to Conventional Feeding, Reduces Risk of Post-Operative Ileus after Elective Hip and Knee Arthroplasty Procedures in Elderly Population: A Protocol for a Parallel Design, Open-Label, Randomized Controlled Trial

**DOI:** 10.29337/ijsp.158

**Published:** 2021-08-09

**Keywords:** Bowel movement, arthroplasty, gum chewing, gut mobility, length of hospital stay, gut motility

## Abstract

**Introduction::**

Postoperative ileus (poi) is defined as a temporary cessation of bowel movement after a surgical procedure. Cessation of bowel movement not only leads to disturbing constipation but also may lead to nausea, loss of appetite, and food intolerance. Literature reports “sham feeding” (gum-chewing) effect as an increase in chewing and saliva which enhances the gastric emptying and overall motility of gut as a cephalic phase of digestion. Therefore, we aim to assess the effect of adding gum-chewing to the conventional postoperative feeding regimen on restoring postoperative bowel function and length of stay in hospital of patients undergoing elective hip arthroplasty.

**Methods and analysis::**

This is a single-center, open-label, parallel design, superiority randomized-controlled trial with 2 treatment arms. The primary and secondary outcomes will be the time interval in hours from the end of surgery until the passage of flatus and the time interval in hours from the end of surgery until the passage of stool. Statistical analysis will be done using STATA software. Length of stay will be calculated by Kaplan–Meier analysis, with unadjusted comparison of groups by Mantel–Cox log rank test. Risk ratios for the time-to-become ileus free and time-to-discharge from hospital will be calculated by Cox regression modeling. P value as 0.05 or less will be taken as significant.

**Ethics And Dissemination::**

This protocol is exempted from Ethical review at this stage however all the required approvals will be taken from the ethical review committee before starting the study. Informed consent will be taken form the patient to enroll him/her in the study. Results of the study will be disseminated to the study participants, public health, and clinical professionals. The results would also be published in a reputable international journal.

**Trial Registration::**

This trial is registered on *clinicaltrials.gov* with ID: NCT04489875.

**Highlights:**

## 1. Introduction

Traditionally, post-operative ileus(poi) is defined as temporary cessation of bowel movement after surgical procedure [1]. Surgical procedures include not only abdominal or colorectal procedures but non abdominal procedures as well, like cesarean sections, arthroplasty, and urological and thoracic procedures [1,2,4]. It is a self-limiting condition for most of patients. It is an under-estimated problem which may affect patient condition directly or indirectly [3]. Cessation of bowel movement does not lead only to a disturbing constipation, but also may lead to nausea, loss of appetite and food intolerance. These patients tend to have more pain scores and dissatisfaction with the surgical management and team [5]. At the moment, no protocol is present to prevent this annoying short-term complication. mechanism behind this condition is caused by decrease in vagal parasympathetic stimulation [3,6]. Here comes the “sham feeding” (gum-chewing) effect where increase chewing and saliva enhance the gastric emptying and overall motility of gut as a cephalic phase of digestion even in non-gastro or colorectal surgeries [2,7,8]. This effect is studied thoroughly in gastric, colorectal, and gynecological procedures. There is scarcity about its effect following orthopedic procedures specifically hip and knee arthroplasty. We therefore hypothesize that sham feeding by using gum chewing will enhance patient’s gut motility, reduce the time to first flatus and stool, enhance the food tolerance and reduce length of hospital stay.

### 1.1 Rationale

With increasing pressure on limited health resources and continually needing to improve the quality of patients’ preoperative experience, interventions with the potential to limit the discomfort of postoperative stay are gaining popularity. The rationale of this study is to accelerate patient recovery and reduce his discomfort and length of hospital stay, which will further reduce the financial burden, by potentially cheap and simple remedy.

### 1.2 Study objectives

Primary objective is to assess the effectiveness of adding gum-chewing to the conventional postoperative feeding regimen on restoring postoperative bowel function in patients undergoing elective hip and knee arthroplasty. Secondary objective is to assess the effect of gum-chewing on length of hospital stay in patients undergoing elective hip arthroplasty.

## 2. Methods

### 2.1 Study design

This study will be a parallel, open-label, superiority randomized-controlled trial at a single hospital. The two arms will be equally allocated on a 1:1 ratio into intervention and control groups.

### 2.2 Interventions and Duration

Behavioral intervention type (Sugarless Gum-chewing) starting the morning after surgery when the patient is fully awake and allowed to start taking feed orally (which usually starts within 6–10 hours after surgery). Patient will be given the gum to chew for 15min minimum duration each time, 3 times/day before the usual time of meal, until the first flatus/passing stool (whatever happen first) in addition to conventional postoperative feeding schedule. Control group will have conventional feeding schedule without added gum. Secondary outcomes will be the postoperative interval until the first passage of stool in hours as well as postoperative hospital stay in days (Surgery to discharge).

### 2.3 Primary and secondary Outcome Measures

Primary outcome will be the time interval in hours from end of surgery till passage of flatus, which is reported subjectively by the patient. Patients will be instructed to make note of the time when flatus is passed first time after surgery. Secondary outcomes will be the postoperative interval until the first passage of stool in hours as well as postoperative hospital stay in days (Surgery to discharge).

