### 2.4 Sample size calculations

To the best of author’s knowledge, this is the first research to study the effect of gum-chewing post-arthroplasty procedure on time to flatus. Literature reported numerous studies on same objective but post abdominal and colorectal surgeries which gave minimum mean time to flatus post-surgery of 67 hours. In arthroplasty no handling of abdominal viscera is there, and we assume time of bowel return to function is considerably less. Hence, considering the rarity of previous literature and the number of cases to be operated in 6 months, investigators decided to recruit and study all eligible patients during the study period from July 2021 to December 2021. Expected number in each arm will be of 50 patients.

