### 2.10 Randomization

After screening and eligibility, patients will be randomly allocated by 1:1 ratio to the Group A gum-chewing (Gum) or Group B control (No gum) groups using a computer-generated randomization sequence by the CTU at the Aga Khan University, which they will provide to the nurse/PI by telephone after patients’ admission in hospital. Patients will be followed from the time they reach the ward after surgery till their hospital discharge, which is usually 7 days.

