### 2.13 Statistical considerations

Categorical data will be summarized as absolute values (percentage). Continuous data will be presented as mean+/– SD if normally distributed and median +/– IQR if not. Length of stay will be calculated by Kaplan–Meier analysis, with unadjusted comparison of groups by Mantel–Cox log rank test. Risk ratios for the time-to-become ileus free and time-to-discharge from hospital will be calculated by Cox regression modeling, considering the following independent variables: age, gender, operation type, diabetes mellitus, preoperative cardiovascular disease (ischemia/heart failure/dysrhythmias), patient-controlled analgesia (PCA) opiate use and presence/absence of chewing gum. P value as 0.05 or less will be taken as significant. Statistical analysis will be done by STATA software version 15.

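### Hospital stay is defined in days but modelled by Cox regression: if that means whole days, ties could weaken this secondary analysis, and recording the discharge time avoids it cheaply

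*Protocol article*

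**What the plan says.** Section 2.3 of the protocol article sets the outcomes. The primary one is in hours: "Primary outcome will be the time interval in hours from end of surgery till passage of flatus". The first secondary outcome is also in hours: "the postoperative interval until the first passage of stool in hours". The other secondary outcome is "postoperative hospital stay in days (Surgery to discharge)". Section 2.2 defines stay in the same way.

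Section 2.13 analyses length of stay by Kaplan–Meier with an unadjusted log-rank test. It adds a covariate-adjusted model: "time-to-discharge from hospital will be calculated by Cox regression modeling". On software it says: "Statistical analysis will be done by STATA software version 15". It names no command, option or tie method.

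The size comes from section 2.4: "Expected number in each arm will be of 50 patients". Section 2.10 follows patients "till their hospital discharge, which is usually 7 days". Section 1.2 makes length of stay the secondary objective. No spread of stay is given anywhere, and no rule for rounding it.

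**The concern.** Cox regression orders patients by event time and works best when few share the same time. Stay is scored on a coarser scale than the other two intervals, and it is the variable on which the time-to-discharge model runs. If it is held as whole days around a usual value of 7, many patients leave on the same value.

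The effect then depends on how the model handles ties. The Breslow approximation shrinks the estimated log hazard ratio when ties are heavy and gives a test that rejects too seldom. The adjusted result for the stated secondary objective could then understate a real effect. Precision is already limited, because the trial size was set by a six-month recruitment window and not by a power calculation.

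The unit of the outcome also governs what is collected. A later analysis plan can choose a tie method, but it cannot recover discharge times that were never written down.

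**Working it through.** **Inputs from the protocol.** 50 per arm (2.4); 1:1 allocation (2.1); usual stay 7 days (2.10); stay in days (2.2, 2.3); Cox and log-rank analyses, p ≤ 0.05 (2.13).

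**Assumptions, because the protocol gives no figures.** Two-sided test; every patient discharged, so 100 events; Weibull stay; true hazard ratio (HR) 1.5, with 1.75 and 1.0 also tried; unadjusted models.

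**The plan's own figure.** The 50 per arm has no stated effect size or power, so there is nothing to reproduce. As a benchmark, with d events and equal arms, power ≈ Φ(|ln HR| × √(d/4) − 1.96). With d = 100 and HR 1.5 this is Φ(0.405 × 5 − 1.96) = Φ(0.07), about 53%. With HR 1.75 it is Φ(0.560 × 5 − 1.96) = Φ(0.84), about 80%. Even ideal timing therefore gives only about even odds at HR 1.5.

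**Simulation.** 3,000 trials per scenario, with stay rounded up to the hour or to the whole day. Results at HR 1.5:

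| Control median; Weibull shape | Distinct days (5th–95th percentile) | Breslow power, hours → days | Breslow mean HR, hours → days | Efron power, hours → days | Log-rank power, hours → days |
|---|---|---|---|---|---|
| 7 days; 2.5 (widest) | 12–16 | 50.8% → 39.9% | 1.51 → 1.43 | 51.3% → 51.1% | 51.9% → 51.3% |
| 7 days; 3.5 | 9–12 | 48.7% → 32.5% | 1.49 → 1.39 | 49.4% → 46.7% | 49.9% → 47.4% |
| 7 days; 5 | 7–10 | 48.8% → 25.4% | 1.49 → 1.35 | 49.9% → 45.4% | 50.4% → 46.8% |
| 5 days; 3 | 8–10 | 50.7% → 31.4% | 1.51 → 1.39 | 51.5% → 48.7% | 52.2% → 50.0% |

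- The Breslow loss runs from 50.8 − 39.9 = 10.9 points to 48.8 − 25.4 = 23.4 points.
- The mean Breslow log HR falls from 0.412 to 0.359 (13%) in the first row and from 0.399 to 0.298 (25%) in the third.
- The Efron loss is 0.2 to 4.5 points and the log-rank loss 0.6 to 3.6 points.
- At HR 1.75, Breslow power falls from 76–79% to 52–69%.
- With no true effect, whole-day Breslow rejects in 1.2–3.1% of trials and whole-day Efron in 4.2–5.0%.

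**Narrower spreads** (2,000 trials each, median 7 days, HR 1.5). With SD 1.9 days, Breslow power falls from 51% to 32% and mean HR from 1.52 to 1.39. With SD 1.3 days, power falls from 50% to 21%, a loss of 29 points, and mean HR from 1.51 to 1.33; about 6 to 9 distinct values occur. Efron on whole days gives 49% and 45% in these two cases.

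**Discharges not spread round the clock.** Real discharges may bunch after ward rounds. When this was built in, timing in hours still gave 45–50% power with Breslow ties, against 21–41% in whole days.

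**The case against.** The strongest reply is that the protocol establishes neither condition on which the loss depends.

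First, a unit of days is not a rounding rule, and if fractional days are kept the loss disappears. Even with whole days the rounding is open: stays of 116 h and 128 h are 4.83 and 5.33 days, which score 5 and 5 to the nearest day, 5 and 6 rounded up, or 4 and 5 rounded down.

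Second, the tie method drives most of the loss, and that is commonly left to an analysis plan, which is not at hand. Naming a software package does not fix the method. What that package does by default is not stated in the protocol, and this point does not rely on it.

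Third, the log-rank test planned for stay loses little. A difference between it and the Cox result would not by itself point to rounding, because the Cox model also adjusts for six covariates.

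All three stand, and they make this a conditional point. Leaving the tie method unnamed would not be a finding on its own. What survives is the outcome unit, which sections 2.2 and 2.3 do state. Hours for flatus and stool beside days for stay makes whole days a natural reading, and that choice decides whether a discharge time is collected at all.

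**Conclusion.** The point holds as a conditional, low-cost improvement. If stay is kept in whole days and the Cox model uses Breslow ties, a true hazard ratio of 1.5 would be estimated on average at about 1.33 to 1.43. Power would drop by roughly 10 to 30 points, and the test would be conservative. With Efron ties the drop is about 0 to 6 points. These figures rest on 50 per arm, complete discharge, Weibull stays with medians of 5 or 7 days, SDs down to 1.3 days, and no covariates.

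A reader might infer three stronger things that the documents do not support.

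- That discharges will collapse onto 6 to 10 values. That count needs a fairly narrow spread, and the protocol gives none; the range tried reaches 16.
- That the Cox analysis is bound to lose most of its power. An SD of 0.95 days does give 14% against 52% with Breslow ties, and 40% with Efron, but nothing in the protocol points to so narrow a spread, to whole days or to Breslow.
- That the trial's main conclusion is at risk. Time to flatus is in hours and unaffected, and the error runs toward no effect, so false positives do not rise.

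**What to change.** In sections 2.2 and 2.3, have the date and clock time of discharge recorded, and define stay as hours from end of surgery to discharge, the same starting point as for flatus. It can still be reported as days to one decimal. In section 2.13, fit the time-to-discharge Cox model on that scale and state Efron or exact handling of ties.

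The cost is one extra clock time to note per patient, one change of wording and one model option. Patients are already followed in hospital until discharge, so no extra patients, visits or procedures are needed. If discharges bunch at certain hours the gain from timing is somewhat smaller, but the choice of tie method still helps.

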### 2.4 Sample size calculations

To the best of author’s knowledge, this is the first research to study the effect of gum-chewing post-arthroplasty procedure on time to flatus. Literature reported numerous studies on same objective but post abdominal and colorectal surgeries which gave minimum mean time to flatus post-surgery of 67 hours. In arthroplasty no handling of abdominal viscera is there, and we assume time of bowel return to function is considerably less. Hence, considering the rarity of previous literature and the number of cases to be operated in 6 months, investigators decided to recruit and study all eligible patients during the study period from July 2021 to December 2021. Expected number in each arm will be of 50 patients.

### 2.5 Selection and enrollment of subjects

#### 2.5.1 Inclusion Criteria

Adult patients aged between 50 to 70 years old undergoing elective primary hip and knee joint replacement surgery with ASA grade I–III and under general anesthetic with/without neuraxial anesthesia will be included.

#### 2.5.2 Exclusion Criteria

Refusal of consent established naso-gastric/gastrostomy feeding, or unsafe swallow due to any neurological disease will be excluded. Investigators will exclude patients with bowel disease other than peptic ulcer, history of chronic constipation more than 3 days before surgery, inability to chew gum due to dental issues, traumatic and revision cases of arthroplasty, adjuvant surgical procedures (Abdominal, thoracic, etc.) beside the primary arthroplasty procedure.

### 2.6 Study Enrollment Procedures

Enrollment will be a continuous process with screening and enrolling eligible patients admitted through clinic electively for primary THR and TKR at the Aga Khan University. Consent will be taken in clinic along with the consent for the procedure by the primary surgeon or his senior resident as per the department policy. Participants will be explained in detail about the procedure as well as the research purpose and intervention detail and duration. We will try to make sure that we purchase the gums from the same vendor for all participants. This study will be funded by the Department of surgery at the Aga Khan University.

### 2.7 Handling of Study Interventions

Sugarless gum will be purchased in bulk after confirming the expiry date and will be kept at the Clinical Trial Unit (CTU) team, dispatching the required gums as per patients’ needs and request from the ward nurse, preferably one at a time. As the intervention is behavioral, it will not be suitable to blind/mask the study intervention.

### 2.8 Adherence Assessment

Compliance of the participants in intervention group will be assessed during normal routine ward rounds at morning and evening. As this is a superiority trial, this adherence along with the dropouts will be incorporated in the analysis phase using with the intention to treat principle as it is the most conservative approach in this scenario and the least to be biased. The patient will be encouraged to keep a diary, otherwise the gum will be provided by the nursing team. As per the hospital policy, nursing team provides all oral medications and help the patients to take them, same procedure will be followed for the gums.

### 2.9 Pre-Randomization Screening

Screening will involve the routine history taking and physical examination by the doctor and nursing staff in the clinic. Screening will not involve performing procedures that are not part of routine patients’ management. Special attention will be given to the dental history and whether patient is able to chew gum or not.

### 2.10 Randomization

After screening and eligibility, patients will be randomly allocated by 1:1 ratio to the Group A gum-chewing (Gum) or Group B control (No gum) groups using a computer-generated randomization sequence by the CTU at the Aga Khan University, which they will provide to the nurse/PI by telephone after patients’ admission in hospital. Patients will be followed from the time they reach the ward after surgery till their hospital discharge, which is usually 7 days.

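### The allocation call is tied only to hospital admission, so anaesthetic, early analgesic and feeding decisions can be taken with the arm already known

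*Protocol article*

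**What the plan says.** All references are to the protocol article.

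- **Disclosure of the arm (2.10).** The trials unit generates a 1:1 sequence, "which they will provide to the nurse/PI by telephone after patients’ admission in hospital". Admission is the only condition on the timing of the call.
- **Type of admission (2.6).** Enrolment consists of "screening and enrolling eligible patients admitted through clinic electively for primary THR and TKR".
- **Follow-up (2.10).** "Patients will be followed from the time they reach the ward after surgery till their hospital discharge". The call is not linked to ward arrival.
- **When the arm is first needed (2.2).** Gum is given "starting the morning after surgery when the patient is fully awake and allowed to start taking feed orally"; oral intake is said usually to begin 6–10 hours after surgery.
- **Discretionary care.** Patients are eligible "under general anesthetic with/without neuraxial anesthesia" (2.5.1), so the block is optional. The Cox covariates in 2.13 include "patient-controlled analgesia (PCA) opiate use and presence/absence of chewing gum". Anaesthetic technique and time of feeding are not on that list.
- **Masking (2.7).** "it will not be suitable to blind/mask the study intervention".
- **Primary outcome (2.3).** Time to first flatus, reported by the patient, counted in hours from end of surgery.

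**The concern.** The primary objective (1.2) is the effect of adding gum to conventional feeding. For that comparison, the rest of the care should not depend on the arm. Gum cannot be masked once it is being chewed, but the allocation can be concealed until then, and section 2.10 does not require this.

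If the call is made soon after admission, the nurse and the PI know the arm through the operation and up to feeding clearance. Sections 2.6 and 3.1, read together, suggest that the PI belongs to the treating team. Under 2.8 the nurses give the oral medications and the gum. The outcome clock is already running, so any arm-related difference in anaesthesia, early analgesia or feeding time would enter the primary outcome and be read as an effect of gum.

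The intention-to-treat principle in 2.8 preserves the randomised groups but does not remove a difference in how they were treated. Adjustment for PCA opiate use helps only in part, because PCA use may itself follow knowledge of the arm.

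**Working it through.** **1. Order of events under the text**

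| Event | Section | Could the arm be known? |
|---|---|---|
| Elective admission | 2.6 | Yes, from here on (2.10) |
| Anaesthesia, block optional | 2.5.1 | Yes |
| End of surgery, clock starts | 2.3 | Yes |
| Early analgesia, including PCA | 2.13 | Yes |
| Clearance for oral feed | 2.2 | Yes |
| First gum, next morning | 2.2 | Must be known |

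The arm is needed only in the last row. A call made after surgery would also satisfy 2.10: the wording allows both.

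**2. The plan's own figure.** Section 2.4 expects 50 patients per arm on feasibility grounds. It gives no effect size, SD or power, so there is nothing to reproduce. For scale, at two-sided 5% (sidedness assumed) and 80% power:

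- standardised difference: (1.960 + 0.842) × √(2/50) = 2.802 × 0.2 = 0.56 SD
- hazard ratio, if all 100 patients have the event: exp(−2.802/√(100 × 0.25)) = exp(−0.560) = 0.57

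**3. A shift in flatus time (illustration).** Assumptions, none from the documents: no gum effect; lognormal flatus time with median 24 or 30 h and log-SD 0.5 or 0.7; log-rank test, 50 v 50, no censoring; every gum patient's time brought forward by a fixed amount. Simulated rate of significant results in favour of gum, across the four combinations of median and log-SD:

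| Shift | False result that gum is faster |
|---|---|
| none | 2.5% nominal |
| 0.5–1 h | about 3–5% |
| 2 h | about 5–9% |

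A shift in the other direction would hide a real effect by the same mechanism.

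**4. An imbalance in one element of care (illustration).** Bias in SD = (difference in use between arms) × (effect of that element in SD). With an assumed 20-point difference and 0.5 SD: 0.20 × 0.5 = 0.10 SD. The standard error is √(2/50) = 0.2, so the test statistic moves by 0.10/0.2 = 0.5. The chance of a significant result in the favoured direction becomes 1 − Φ(1.96 − 0.5) = 0.072, against 0.025.

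**5. Flatus before a late call.** Under the same lognormal assumptions, the proportion with flatus by time t is Φ(ln(t/median)/log-SD).

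- By 12 h: from Φ(ln(12/30)/0.5) = 3% to Φ(ln(12/24)/0.7) = 16%
- By 16 h: from Φ(ln(16/30)/0.5) = 10% to Φ(ln(16/24)/0.7) = 28%

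These patients cannot be ignored when the call is moved.

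**The case against.** **The text permits an early call but does not require one.** This stands. Central telephone allocation is also sound concealment up to the point of disclosure, and the full protocol may set the hour more tightly. But the article does state when the arm is disclosed, and that condition leaves room for a call before surgery.

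**Nobody says the anaesthetist is told.** This also stands. The named recipients are the nurse and the PI, so the route through anaesthesia is an inference. Equally, nothing in an open-label trial keeps the arm from the rest of the team.

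**A reader might infer that the bias favours gum**, because gum waits for feeding clearance and staff might clear gum patients sooner. The documents do not support this. Section 2.2 ties gum to the morning after surgery and to mealtimes as well as to clearance, so earlier clearance need not bring gum forward. For block and analgesia, no direction can be read from the text.

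**A reader might also carry the illustration to shifts of 4–6 h**, where the false-positive rate grows much larger. The usual feeding window in 2.2 runs from 6 to 10 h. Even with every gum patient cleared at 6 h and every control at 10 h, feeding would differ by 10 − 6 = 4 h. Flatus would have to move by as much as that extreme, or more, in every patient. Nothing in the documents suggests it.

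**PCA use is already adjusted for.** True, within the limit that it may be affected by allocation. Anaesthetic technique and feeding time are not on the list.

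**Conclusion.** The point holds as an avoidable looseness in 2.10. The arm may be disclosed before surgery, well before it is needed, in an open-label trial whose clock starts at end of surgery. Performance bias through block, early analgesia or feeding clearance is possible. The documents do not show that it will occur, which way it would run or how large it would be.

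The illustrative size is modest: with a shift of up to 2 h towards gum, about 3–9% false results in that direction against 2.5%. This rests wholly on the assumed distribution and shift. The change is worth making because it is cheap and because the planned analysis cannot fully undo such a difference afterwards.

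**What to change.** In 2.10, state that:

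1. The trials unit assigns each patient an allocation from the pre-generated sequence at registration and keeps it concealed. The patient counts as randomised from that point.
2. The unit releases the arm by telephone only after surgery, once the treating team has recorded, under its usual practice, that the patient may take oral feed.
3. The clock still starts at end of surgery. Every randomised patient is analysed in the allocated arm, including those who pass flatus before the call and those never cleared to feed.

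Consent, screening, and anaesthetic and feeding practice stay as they are; only the time at which the arm becomes known changes.

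**Cost.** A few sentences, and a trials unit that can be reached the morning after surgery. Some patients will have passed flatus before release (3–16% by 12 h and 10–28% by 16 h under the assumptions above). They are expected equally in both arms and dilute the contrast. Much of this dilution is already in the plan, because gum does not start before the morning after surgery.

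**Limit.** Only decisions made before release are protected. Later analgesia and feeding, and the patient's own report of flatus, remain open-label.
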